## Statistical methods

### Statistical methods for primary and secondary outcomes {20a}

This analysis plan provides the initial framework for examining primary and secondary outcomes. A significance level of 0.05 will be applied unless otherwise specified, with corrections for multiple comparisons (e.g., Bonferroni) used when necessary. All analyses will follow the intention-to-treat principle, accounting for the nested structure within centers if appropriate. The analyses outlined here may be subject to minor modifications based on advancements in the field. Should any deviations from the original plan occur, these will be clearly documented and justified. Our reporting will adhere to the guidelines set by the CONSORT statement [98].

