#### Identification of predictors of response and remission

Another aim of the study is to identify combinations of patient characteristics and behaviors that predict treatment response and remission. To achieve this, we will conduct AIC penalized bootstrapped stepwise logistic regression in both forward and backward directions, examining predictors of remission and treatment response in two separate models. The examined predictors will include:Demographic Factors: *Age, Sex, Educational Level*Clinical Characteristics: *Clinical Diagnosis, Severity of Depressive Symptoms, Diurnal Variation in Affect*Sleep-Related Factors: *Subjective Sleep Quality, Sleep Efficiency, Sleep Duration, Sleep Onset Latency, Midsleep Timing, Wake after Sleep Onset, Severity of Insomnia Symptoms, Energy Levels*Circadian Factors: *Circadian Phase, Intradaily Stability, Intradaily Variability, Phase Angle Difference between DLMO and Sleep Onset, chronotype.*Light-related parameters: *Light Sensitivity*Expectations: *Expectations of Treatment*

All predictors will be measured either at intake or during the baseline week. Prior to the stepwise regression analysis, we will assess multicollinearity by calculating the Pearson correlation coefficient and Variance Inflation Factor (VIF). Variables exhibiting a Pearson correlation coefficient greater than 0.8 or a VIF score exceeding 10 will be removed to mitigate multicollinearity and examined separately. A final competitive regression model will be run with all significant predictors.

To ensure the robustness of our models, we will run 1000 bootstrap samples and retain predictors that are significant in at least 60% of the bootstrapped samples. We will also calculate partial R-squared values for all predictors in the regression models to quantify the proportion of variance in the dependent variable explained by each specific independent variable while controlling for the influence of others. Finally, we will conduct variance partitioning to investigate the unique and shared variance explained by the predictors. By comparing the explained variance from regression models of individual predictors against those with combinations of predictors, we will compute both unique and shared variance. The vegan package in R will be used for variance partitioning, and results will be visualized using Euler plots from the Euler package.

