To benchmark the added value the *LightCafé* and the personalized chronotherapeutic interventions, we contrast the two administration strategies against an active home-based control (Light@Home). Opting for Light@Home as our control arm reflects a pragmatic choice: although it precludes attribution of observed effects solely to light exposure, it provides a realistic comparator that mirrors how many patients already receive BLT and is therefore a valuable comparator in our search for optimization of administration. It should however be noted that even though we adhere to Dutch BLT guidelines for depression, the field still lacks consensus on optimal BLT dosing—specifically wavelength, intensity, and overall treatment duration—so true optimized delivery of BLT still warrants further investigation.

Besides these pragmatic, real-life objectives, our study also aims to identify individual characteristics predicting responses to BLT, examining a range of socio-demographic, clinical, sleep-related, circadian, and light-related factors. We will employ advanced statistical techniques to uncover strong predictors of positive outcomes, enhancing clinical decision-making and paving the way for a more personalized approach to BLT. The trial also explores the mechanisms underlying BLT’s efficacy through mediation analysis, assessing whether and how changes in circadian rhythm mediate its antidepressant effects. Using EMA data analyzed via random-intercept cross-lagged panel modelling (RI-CLPM), we will capture real-time fluctuations in mood, sleep, and energy levels, clarifying whether BLT primarily targets mood, sleep, energy, or a combination of these factors. Neurobiological analyses via MRI will further elucidate structural and functional brain changes associated with BLT, including assessments of connectivity and activity patterns.

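### The 60% bootstrap retention rule for predictors of response is uncalibrated: with no true predictor it still names at least one in roughly 45–60% of trials per outcome model

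*Protocol article*

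**What the plan says.** The section on identification of predictors of response and remission states: "we will conduct AIC penalized bootstrapped stepwise logistic regression in both forward and backward directions". There is one model for each of the two outcomes. The section lists 21 candidates: 3 demographic, 3 clinical, 8 sleep-related ("Subjective Sleep Quality, Sleep Efficiency, Sleep Duration, Sleep Onset Latency, Midsleep Timing, Wake after Sleep Onset, Severity of Insomnia Symptoms, Energy Levels"), 5 circadian ("Circadian Phase, Intradaily Stability, Intradaily Variability, Phase Angle Difference between DLMO and Sleep Onset, chronotype"), 1 light-related and 1 on expectations. The only pre-filter removes collinear variables (pairwise correlation above 0.8 or variance inflation factor above 10).

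Retention is then fixed: "we will run 1000 bootstrap samples and retain predictors that are significant in at least 60% of the bootstrapped samples". The same section says "A final competitive regression model will be run with all significant predictors" and adds partial R-squared and variance partitioning. It gives no basis for 60%, no false-selection rate, no validation sample and no optimism correction.

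The general statement in section {20a} is: "A significance level of 0.05 will be applied unless otherwise specified, with corrections for multiple comparisons (e.g., Bonferroni) used when necessary". It does not say whether this analysis is one where correction is necessary. The Discussion sets the ambition: "We will employ advanced statistical techniques to uncover strong predictors of positive outcomes, enhancing clinical decision-making".

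**The concern.** A bootstrap frequency measures how stably a result recurs when the same data are resampled. It does not test whether the result is real. An association that arose by chance in the trial is present in the data from which every resample is drawn, so it tends to recur. Stepwise selection by AIC within each resample adds overfitting.

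Identifying predictors is the first secondary objective, and the Introduction says it should let clinicians stratify patients by likelihood of response. A predictor described as robust because it passed this filter would carry more weight than the filter can support. Its p-value would be too small and its explained variance too large, because both come from the data that selected it.

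**Working it through.** The plan states no error rate for this rule, so there is no figure to reproduce.

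**Inputs from the Protocol article.** 21 candidates, two outcome models, significance level 0.05 (taken as two-sided), cut-off 60%. The sample size section gives 210 evaluable and 231 enrolled; 231 × 0.9 ≈ 208 after 10% drop-out. The EMA subsample is 120 and the saliva subsample is 72.

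**Assumptions not in the document.** Response rate 30–50%; correlation between predictors 0–0.3; no predictor truly related to outcome (global null).

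**Step 1. What 60% means for one predictor.** If the resampled z is roughly normal around the observed z with variance 1, significance in at least 60% of resamples needs |z| ≥ 1.960 + 0.253 = 2.213, that is p ≈ 0.027.

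**Step 2. Many candidates, no stepwise effect.** With k independent candidates the chance of at least one false retention is 1 − (1 − 0.0269)^k.
- k = 21: 1 − 0.564 ≈ 44%
- k = 17: 1 − 0.629 ≈ 37%
- k = 16: 1 − 0.646 ≈ 35%

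**Step 3. How many candidates exist in the full sample.** Energy levels and diurnal variation in affect come from EMA (120 participants). Phase angle and light sensitivity come from saliva (72). That leaves 21 − 4 = 17, or 16 if circadian phase means melatonin onset. This count takes the sleep candidates from actigraphy and questionnaires, because the sleep diary is also delivered through EMA.

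**Step 4. Simulation of the written procedure under the global null.** A predictor counts as significant in a resample if stepwise AIC keeps it with Wald p<0.05. It is retained if that happens in at least 60% of all resamples. The table covers one outcome model with 600 simulated trials per row; the first row used 1,000 resamples per trial, the others 200.

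| Setting, all 21 candidates | At least one false predictor |
|---|---|
| n=210, 50% response, uncorrelated | 55% (SE 2 points) |
| n=210, 30% response | 60% |
| n=210, correlation 0.3 | 60% |
| n=210, stepwise started from the null model | 57% |
| n=231, 50% response | 56% |

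The mean number of false predictors was 0.8 to 1.0 per model. Without the bootstrap filter, stepwise selection with p<0.05 gave 72% in the first setting. The filter therefore helps, but only from 72% to 55%.

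Other readings of the rule at n=210 with 21 candidates gave 44% (single-predictor tests), 48% (full model without stepwise) and 93% (any predictor kept by AIC counted as significant).

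With 17 candidates, n=208, 40% response and correlation 0.1, the rate was 43% (120 simulated trials). Linear-model approximations with 16–17 candidates at n=210 gave 44–47%. Across all runs with 16–17 candidates the range was about 43–56%.

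**Step 5. Both outcomes.** If the two models were independent, per-model rates of 43% and 56% would give 1 − 0.57² ≈ 68% and 1 − 0.44² ≈ 81%. Response and remission are correlated, which lowers this. One approximation with correlated outcomes gave about 70%.

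**Step 6. The cut-off that would hold 5% in one model.** Analytically, for 21 candidates, p = 1 − 0.95^(1/21) = 0.0024, so |z| = 3.03 and the share is Φ(3.03 − 1.96) ≈ 0.86. In simulation at n=210 the 95th percentile of the largest null share was 0.90; other runs gave 0.87–0.93.

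**The case against.** **Section {20a} already provides for multiplicity.** It does so in general terms, and a strict application would lower the rate. A reader might infer from the predictor section that the plan has no multiplicity provision at all; that goes too far. What stands is that the provision is conditional and the retention rule carries no correction.

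**The global null is the worst case.** The Introduction cites earlier findings for some candidates, such as diurnal mood variation, chronotype and education. Fair: the figures describe how the rule behaves on noise, and performance with some real predictors was not examined.

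**This is a secondary aim and the rule is about stability.** A 5% family-wise target over both outcomes is partly a choice. That also stands. But the section on additional analyses labels other work exploratory, and this analysis carries no such label.

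**The full-sample headline.** One might infer that a single model will more often than not name a false predictor at full sample size. The documents do not support this, because all 21 candidates are not measured in 210 patients; with 16–17 the range straddles one half.

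**The small subsample.** One might also infer that a complete-case model in the 72 saliva participants is worse still. That cannot be shown. Under the plain reading, simulated rates there were about 5% or 30%, depending on whether the stepwise search starts from the full or the null model, because fits separate and Wald tests fail.

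**Order of steps.** The sentence on the final competitive model comes before the bootstrap paragraph, so a refit of the bootstrap-retained set is an inference. Either way, the final model uses the data that chose its predictors.

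**Conclusion.** The point holds in this form. The 60% rule is a fixed, unjustified cut-off that does not give the robustness claimed for it. Under a global null it names at least one false predictor in roughly 45–60% of trials per outcome model at about 210 patients: about 43–56% with the 16–17 candidates measured in everyone, and about 55–60% if all 21 were available. Over both models the chance is higher.

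These figures rest on assumed response rates of 30–50%, assumed correlations of 0–0.3, and the plain reading of the rule. The consequence is limited to the credibility of the named predictors. The comparison of the three treatment arms is not touched.

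**What to change.** In the section on identification of predictors:

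1. Permute the outcome, rerun the whole collinearity screen, stepwise selection and bootstrap on each permuted dataset, and set the retention cut-off from that null distribution at a false-selection rate stated in advance. For a 5% chance of any false predictor in one model, expect a cut-off of about 0.85–0.93. State whether the rate applies per model or over response and remission together.
2. At minimum, keep 60% but report its permutation-based false-selection rate beside the results.
3. Report bootstrap optimism-corrected discrimination and R-squared, with the selection repeated in each resample. Do not present the final model's ordinary p-values or partial R-squared as evidence.

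The cost is computing time, a few sentences, and lower sensitivity to weak true predictors. Section {20a} allows documented modifications to the analyses, and the trial is still enrolling.

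### The explained variance of the response and remission predictors is computed on the same patients that selected them, with no correction, so it is biased upward even for real predictors

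*Protocol article*

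**What the plan says.** All of the procedure stands in the protocol article, under Identification of predictors of response and remission.

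- **Aim.** The analysis is meant to "identify combinations of patient characteristics and behaviors that predict treatment response and remission", with separate models for the two outcomes.
- **Candidates.** The list has 3 demographic, 3 clinical, 8 sleep-related, 5 circadian, 1 light-related and 1 expectation item, 21 in all.
- **Selection.** The method is "AIC penalized bootstrapped stepwise logistic regression in both forward and backward directions", after a collinearity screen. The retention rule reads: "we will run 1000 bootstrap samples and retain predictors that are significant in at least 60% of the bootstrapped samples".
- **Final model.** "A final competitive regression model will be run with all significant predictors".
- **Reported quantities.** The plan will "calculate partial R-squared values for all predictors in the regression models". It will also derive unique and shared variance by "comparing the explained variance from regression models of individual predictors against those with combinations of predictors", shown as Euler plots.

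The section names no hold-out sample, cross-validation, optimism correction or shrinkage.

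**The concern.** A predictor that survives stepwise selection and a significance-based retention rule does so partly because its association happened to be strong in these patients. Explained variance computed in the same patients carries that luck with it. A false predictor then shows a positive share although its true share is zero. A real predictor shows a share that is too large, because it is more likely to be kept in samples that overstate it. The second effect would remain even if no false predictor were ever retained.

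Prediction of response is a secondary objective under Objectives. The quantities at stake are the ones the section would print for each predictor, and a reader would naturally take them as a measure of how much each predictor matters.

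**Working it through.** **No figure of the plan to reproduce.** The section states no sample size, event rate or R-squared. The check is a simulation of the stated rule.

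**Inputs from the protocol article**
- 21 candidates (counted above) and significance level 0.05 (Statistical methods; two-sided assumed).
- Whole sample: 210 analysed, 210 × 1.10 = 231 enrolled (Sample size).
- Subsamples: momentary assessment in 120 patients, melatonin in 72 (Data collection and management). Phase angle to melatonin onset and light sensitivity need melatonin data. Complete cases on all 21 candidates therefore cannot exceed 72, and are fewer if the two subsamples overlap only in part.

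**Inputs assumed, not in the documents**
- 40% events, all candidates continuous, pairwise correlation 0.2.
- Either no true predictor, or three with log-odds 0.3 per SD (odds ratio exp(0.3) = 1.35).
- 100 bootstrap samples per trial in place of 1000, and about 120 simulated trials per setting, so the Monte Carlo standard error of a proportion is about 0.05.

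**Analytic anchor.** With no true predictor and all 21 fitted unselected, expected linear R-squared is 21/(n−1):
- n=210: 21/209 = 0.100 (simulated 0.099)
- n=120: 21/119 = 0.176 (simulated 0.188)
- n=72: 21/71 = 0.296 (simulated 0.324)

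**No true predictor, 60% rule applied (main run)**

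| n | trials keeping at least one | apparent R² in those trials | population R² |
|---|---|---|---|
| 210 | 57% | 0.039 | 0 |
| 120 | 62% | 0.074 | 0 |
| 72 | 57% | 0.088 | 0 |

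These are Brier-type values. On the Nagelkerke scale, other runs gave 0.047 to 0.057 at n=210 and 0.101 at n=72. Hence the ranges of about 4 to 6% and about 9 to 11%. The share of trials keeping something is less stable at n=72: 45% with a 30% event rate, and 36% in another run with 40% events.

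Averaged over all trials, including those that keep nothing, the apparent value at n=210 is 0.023. Linear adjusted R-squared after selection also stays positive (0.017 at n=210, 0.037 at n=120), so adjusting for the number of retained terms does not remove the effect.

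**Three true predictors, retained set as a whole (Nagelkerke).** The right comparator is the population R-squared of the *same retained set*, because it excludes error in the fitted coefficients.
- n=210: 0.132 apparent against 0.061 (0.11 against 0.05 in a second run)
- n=72: 0.211 apparent against 0.041

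**Three true predictors, partial R-squared of those retained**

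| n | apparent | population | ratio |
|---|---|---|---|
| 210 | 0.060 | 0.034 | 0.060/0.034 = 1.8 |
| 120 | 0.096 | 0.040 | 0.096/0.040 = 2.4 |
| 72 | 0.135 | 0.039 | 0.135/0.039 = 3.5 |

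A second run gave about 0.05 against 0.025 at n=210 (ratio 2.0) and about 0.10 against 0.03 at n=72 (ratio 3.3).

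**Stronger signal.** At n=210 with log-odds 0.47, model R-squared was 0.235 apparent against 0.174 in the population, a ratio of 1.35. The bias shrinks as true effects grow.

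**Does the remedy work?** Five-fold cross-validation that repeated the selection in each fold gave mean R-squared of −0.031, −0.065 and −0.008 with no true predictor (n=210, 120, 72), at or below zero as it should be. With three true predictors at n=210 it gave 0.005, against 0.019 in 20,000 new patients and 0.093 apparent (Brier-type, all trials). At n=72 it was less exact: 0.003 against −0.037 in new patients, still far from the apparent 0.088.

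**The case against.** **It is an omission in an article.** Statistical methods calls the text an initial framework, and internal validation of a secondary model is often left to the analysis plan. That would carry weight if the article were silent on method. It is not: it fixes the selection rule, the number of bootstrap samples, the threshold, the variance measures and the plots. Followed as written, those steps yield biased figures.

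**The 60% rule already handles it.** It reduces the bias. With no true predictor at n=210, the unfiltered stepwise set gives a mean apparent R-squared of 0.062, and the filtered set 0.023. It does not remove the bias, and every ratio above includes the rule.

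**Comparison with new patients exaggerates.** This stands. R-squared in new patients also falls because coefficients are estimated with error, so that gap is not all inflation. The ratios above use the population value of the same retained set instead.

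**Stronger readings that a reader might infer, and that the documents do not support**
- *That explained variance will be grossly inflated in every case.* At n=210 with no signal the average excess is about 2 points, or about 4 to 6 when something is kept.
- *That the authors base clinical decisions on explained variance.* The Discussion hopes to "uncover strong predictors of positive outcomes, enhancing clinical decision-making". It speaks of predictors and does not mention explained variance.
- *That the plan ranks predictor groups by R-squared.* It compares individual predictors with combinations and announces no group-level figure.

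**Conclusion.** The concern holds as a point of moderate weight about a secondary objective; the primary MADRS comparison is untouched. Partial R-squared and unique and shared variance, computed as described, are biased upward by the plan's own selection rule, for real predictors as well as false ones.

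The size rests on the assumed event rate, correlations, effect sizes and R-squared definition, none of which the article gives. It is a few points at the full sample size. It is most serious for weak to modest effects and for any model that includes the melatonin-based candidates, where at most 72 patients have complete data. The direction of the bias held in every setting examined; the exact multiples should be read as approximate.

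**What to change.** In Identification of predictors of response and remission, add internal validation of each final model (response and remission) by repeated cross-validation. Every training fold should repeat the collinearity screen, the stepwise selection and the 60% rule. Report the held-out explained variance as the main estimate of how well the model predicts.

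Keep the in-sample partial R-squared, variance partitioning and Euler plots as description. Label them *apparent* (not corrected for selection), show them beside the held-out value, and do not use them to claim predictive value. They should not be rebuilt from held-out values: these can be negative, which an Euler plot cannot show, and the retained set may differ between folds.

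The cost is a short addition to the text, some computing time and a less favourable reported explained variance. No new data or patients are needed.

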### Neural Correlates of BLT

#### Preprocessing and data cleaning

Neuroimaging data (functional and structural) will be visually inspected and subjects with artifacts in the images (e.g., based on movement) will be discarded from the analysis. All brain data will be transformed into the brain imaging data structure (BIDS), in order to be shareable and easily accessible for further steps [100]. Data will then be pre-processed and analyzed using existing standardized neuroimaging pipelines depending on the data types (structural or functional). Functional data will be pre-processed using fMRIPrep [101, 102].

#### Neuroimaging data types and software

We will gather three types of data based on the outputs from the four scanning sequences employed.

The first type is structural imaging data, which includes measures of gray matter (GM), white matter (WM), and LGI. This data will be pre-processed using the standardized FreeSurfer analysis pipeline (http://surfer.nmr.mgh.harvard.edu/). The preprocessing steps are automated and briefly include motion correction, intensity normalization, skull striping, segmentation in GM and WM, and inflation of these surfaces. Afterwards the extraction of specific GM and WM metrics is performed, this encompasses, among others, THK, VOL, SA, and LGI.

The second type is WM tract data obtained from DTI sequence. We will focus on extracting properties of the main WM tracts, specifically FA and MD. For this, we will use a probabilistic tracking analysis approach implemented as a standardized analysis pipeline of Freesurfer, namely the TRActs Constrained by UnderLying Anatomy (TRACULA) [103, 104].

The third type is functional connectivity data based on the BOLD signal of the resting state functional scan; it will allow to assess the functional connectivity properties of certain brain networks under resting state conditions using standardized pipelines from the CONN toolbox [104].

